### ***Quantitative outcomes evaluation:***

*Study Population/Recruitment:* All consecutive adults presenting to the mental health clinics at the four selected health centers for an initial visit between approximately October 2014 and January 2015, who have been diagnosed with a major mental or neurologic disorder, will be invited to participate in the quantitative outcomes evaluation. The mental health clinic day occurs once weekly as designated by the health center schedule. On that day, the clinician researcher will be available at the health center for enrollment in the research evaluation. Patients will be informed by the health center nurse, the MESH mentor and/or the clinician researcher present at the clinic, that a research evaluation of the mental health program will be occurring. If patients agree, the trained mental health clinician researcher will explain the evaluation further to the patient and determine whether the patient is willing to participate. Additionally, patients with a mental disorder who arrive at the clinic on a non-designated mental health clinic day will also be informed of the program evaluation by the health center nurse, and will be invited to return to participate the following week on the day that the clinician researcher will be present. Written informed assent from the patient and consent from his/her designated proxy will be obtained before data collection begins.

*Data collection, measures and outcomes:* The primary outcomes will be mental health status and daily functioning, measured at first visit, eight weeks and four months after beginning participation in the MESH MH program. Outcome measures will be determined by two clinician administered scales: the General Health Questionnaire (GHQ-12) and the World Health Organization Disability Assessment Scale (WHO-DAS 2.0 Brief). These scales have demonstrated high levels of validity and reliability and have been used extensively in developing countries. A brief economic status questionnaire for patients with mental disorders, adapted from other resource limited contexts, will also be administered. All instruments will be translated into Kinyarwanda and back translated prior to implementation. The symptom and functioning scales will be used prior to the study by staff at the district mental health clinic and a small convenience sample of patients to ensure face validity.

The three scales will be administered by the trained clinician researcher who will be available on the designated mental health clinic days for questionnaire administration. If the clinician researcher determines that a patient is unable to offer adequate answers to questions secondary to severe mental illness (e.g. the patient exhibits clinical signs of severe psychosis such as disorganized thinking), the primary family member in attendance at the clinic with the patient

will be used as a proxy to answer questions, and the fact that a proxy has been used will be recorded. Demographic information as well as self-reported treatment status (new to treatment or received previous treatment) will be recorded. The PI will periodically check all completed questionnaires to ensure data quality and re-interview a random selection of respondents to verify data reliability.

*Follow up:* The mental health clinician researcher will maintain a list of patients who participated in the baseline data collection. Patients will be re-interviewed at eight week and four month follow up, on their return for follow up to the health center. For patients who do not return to follow-up, a community health worker in their village will be contacted to visit the patient and encourage the patient to return to care (as is routine practice in the current health system). Patients who return will be re-interviewed at eight week and four month follow up. The interviewer will not have sight of the previous questionnaires on follow up interviews.

*Analysis:* All participating patients will be included in the analysis. Patients who do not return for follow up will not be re-interviewed but will be included in final data analysis and we will examine baseline differences among those who do and do not complete follow-up interviews. Among patients who receive a score of  $> 2$  on the WHO DAS-II (indicating non-zero baseline disability) and a score of  $\geq 3$  on the GHQ-12 (indicating psychiatric caseness), we will calculate the percent of patients who experience clinically significant reductions in score (25% for the GHQ-12 and 20% for WHO-DAS-II Brief). Since there is currently no information on the percentage of individuals anticipated to achieve these score reductions within our population, we will assume this to be 50% (the most statistically conservative for sample size calculations – we expect this percentage to be greater which will increase our precisions). A sample size of 96 patients will allow us to estimate these proportions and 95% confidence intervals with precision of  $\pm 10$ . Assuming a drop-out rate of 20%, the minimum sample size for enrollment in the study will be 116. In order to stratify outcomes by characteristics such as age, gender, health center, diagnosis, and whether the patient is newly diagnosed or has previously been treated for a mental disorder, we will enroll as many patients are willing to participate (an estimate of 300 patients). We will use multivariable logistic regression to identify covariates associated with improved scores. Among individuals with low GHQ-12 and WHO-DAS-II Brief scores we will calculate within-person mean score change at eight weeks and four months. We will also calculate the percentage of patients who report improvements on the economic questionnaire and calculate mean score changes for individual responses.

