## **Limitations**

There are limitations to the study design. First, this project endeavors to evaluate the plausibility that the MESH MH program contributes to improved clinical and functional outcomes among patients participating in the program, but it does not include a control group. The ability to draw causal inferences about the effectiveness of the MESH MH program in improving patient outcomes will therefore be limited. The use of program process indicators as an adjunct to the qualitative and quantitative outcome assessment will also help to ensure confidence that the MESH MH program has been implemented as intended at studied health centers. The addition of the process evaluation will strengthen the plausibility that any observed clinical changes could be attributed to the MESH MH program.

A second limitation is that the MESH mental health program is currently being implemented in public health centers in only one district in Rwanda which is well supported by Partners In Health (PIH). Thus, health system programming results may not be generalizable across all districts. For example, the in-country PIH psychiatrist will play an intensive role in supervision and monitoring of the program; this level of supervision may not be feasible in other districts and could influence the quality of delivery of the program, as well as patient outcomes. However, this plausibility evaluation will be the first report on service uptake, care quality and patient outcomes of a newly implemented supervised mental health program at the health center level, which may lead to further rigorous testing of the effectiveness of the intervention as it is scaled to other health centers and districts in Rwanda.

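### Change on the GHQ-12 and WHO-DAS is reported only in groups split by the baseline score itself, with no whole-cohort change and no count of worsening

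*Protocol*

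**What the plan says.** All of this is in the Protocol, Quantitative outcomes evaluation, unless stated otherwise.

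- Primary outcomes: "The primary outcomes will be mental health status and daily functioning, measured at first visit, eight weeks and four months". The instruments are the GHQ-12 and the WHO-DAS 2.0 Brief.
- Who enters the percent-improved analysis: patients scoring > 2 "on the WHO DAS-II (indicating non-zero baseline disability) and a score of" ≥ 3 "on the GHQ-12 (indicating psychiatric caseness").
- What is calculated in them: "we will calculate the percent of patients who experience clinically significant reductions in score (25% for the GHQ-12 and 20% for WHO-DAS-II Brief").
- What is calculated in the others: "Among individuals with low GHQ-12 and WHO-DAS-II Brief scores we will calculate within-person mean score change at eight weeks and four months".
- Covariates: "We will use multivariable logistic regression to identify covariates associated with improved scores".
- Sample size: 96 patients, to estimate these proportions to within ±10 points. A 50% response is assumed and a higher one expected.
- The Limitations section says of the project: "but it does not include a control group". It concludes that causal inference will be limited.

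For the two primary scales, the text specifies no mean change above the cut-offs or in the whole cohort, no percent worsened and no reference rate of improvement. Regression to the mean is not mentioned. The economic questionnaire is treated differently: its percent improved and mean changes carry no baseline restriction.

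**The concern.** Each patient is sorted by a baseline score that contains measurement error and day-to-day variation, and change is then counted from that same score. Three things follow even when patients do not change.

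- Above the cut-offs only falls are counted, so any fluctuation of sufficient size downward is a response, and the matching upward moves are never reported.
- Patients whose baseline was high by chance are kept and those whose baseline was low by chance are removed, which tilts the retained group toward falls.
- The only group given a mean change sits near the floor of the scale, where scores have little room to do anything but rise.

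The two summaries are therefore pulled in opposite directions, and the plan specifies no neutral figure to read them against. This matters because the Executive Summary and the Program Research Evaluation section require documented improvement in clinical outcomes before national scale-up is considered, and the Dissemination section ties scale-up recommendations to positive results.

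**Working it through.** **1. The plan's own figure.** n = 1.96² × 0.5 × 0.5 / 0.10² = 3.8416 × 0.25 / 0.01 = 96.04, which reproduces 96. The study is sized on the percent improved.

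**2. How small a fall counts.** On integer scoring (assumed), the points needed are the percentage times the baseline, rounded up.
- GHQ-12: baseline 3 gives 0.75 → 1; 4 gives 1.00 → 1; 5 gives 1.25 → 2.
- WHO-DAS: baseline 3 gives 0.6 → 1; 5 gives 1.0 → 1; 6 gives 1.2 → 2.

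Just above the cut-offs, a one-point fall is a response.

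**3. Simulation with no true change.** The cut-offs and the 25% and 20% thresholds come from the protocol. Everything else is assumed: reliability ρ = 0.7; GHQ-12 scored 0–12 with SD 3.3; WHO-DAS scored 0–48 with SD 9; the baseline means shown below. Low scorers are taken as those below the cut-off.

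Model: Y₁ = m + s(√ρ·T + √(1−ρ)·E₁) and Y₂ = m + s(√ρ·T + √(1−ρ)·E₂), with T, E₁ and E₂ independent standard normal. Scores are rounded and truncated to the scale, with 400,000 patients per setting. Each scale is selected on its own cut-off. In the unselected column, a baseline of 0 counts as not improved.

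| Scale, baseline mean | Improved, above cut-off | Improved, unselected | Added by selection | Worsened by same points, above cut-off | Mean change, low scorers | Mean change, all |
|---|---|---|---|---|---|---|
| GHQ-12, 7 | 25% | 24% | 1 | 24% | +1.8 | 0.0 |
| GHQ-12, 5.5 | 31% | 28% | 3 | 25% | +1.4 | 0.0 |
| GHQ-12, 4 | 38% | 31% | 7 | 25% | +1.1 | 0.0 |
| WHO-DAS, 20 | 28% | 27% | 1 | 30% | +5.5 | 0.0 |
| WHO-DAS, 15 | 34% | 31% | 3 | 32% | +4.2 | 0.0 |
| WHO-DAS, 10 | 41% | 34% | 7 | 32% | +3.1 | 0.0 |

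Repeat runs agree to about one percentage point. Mean drift above the cut-offs is small: at most about 0.5 GHQ-12 points and 0.8 WHO-DAS points downward.

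**4. Sensitivity.**
- Over ρ = 0.6 to 0.9 the percent improved above the cut-offs runs from 14% to 42% (GHQ-12) and from 16% to 43% (WHO-DAS).
- A second set of assumptions required both cut-offs jointly, as the text is worded. It used GHQ-12 mean/SD 4/3.5, 6/3.5 and 8/3; WHO-DAS 10/9, 16/10 and 22/10; a between-scale correlation of 0.6; and ρ = 0.5 to 0.9. The percent improved was 9–46% and 16–47%. Low scorers rose by 0.4 to 3.3 GHQ-12 points and 1.1 to 10.2 WHO-DAS points. Whole-cohort mean change stayed within about 0.03 of zero.
- In that set at ρ = 0.7, the mildest population gave 39% improved against 24% worsened by 25% on the GHQ-12. The most severe gave 19% against 21%.
- At ρ = 1 every entry is 0.

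**5. Against the plan's expectation.** A result of 50% ± 10 spans 40–60%. The top of the no-change range (41% in the table, 46–47% in the wider set) falls inside that interval; most of the range lies below it.

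**The case against.** A reader might infer that regression to the mean, through selection of high scorers, produces the main result. The documents do not support that. The cut-offs are low: the protocol describes them as non-zero disability and caseness, in patients already diagnosed with a major disorder. In the settings tabulated, most patients exceed them, and selection explains only about 1–7 points of the percent improved. In the more severe settings improvers do not outnumber worseners. A floor is also needed for a percent reduction to have meaning, since a score of 0 cannot fall. All of this stands.

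It also stands that the documents give no baseline means, SDs, reliability or scoring range, so every size here is assumed. The zero whole-cohort change is built into a simulation with no true change. Calling the percent improved the main result is an inference from the sample size basis.

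A reader might add that the logistic regression on improved scores wastes power at 96 patients. That should not be argued: 96 is the precision minimum, and the protocol plans to enrol an estimated 300 so that outcomes can be examined by patient characteristics.

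Two further defences do not hold. The section does say that every participant enters the analysis, and it does not forbid a whole-cohort mean. However, it goes on to fix which summary is given to which group, so this is more than detail left to an analysis plan. The Limitations section concedes the missing control group, but the split by baseline is a separate problem that can be avoided without a control group.

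**Conclusion.** The point holds as a should-fix. As written, the protocol reports the two primary scales in groups defined by the baseline score, with only falls counted in one group and only mean change in the other. With no true change and reliability 0.7, about 25–38% (GHQ-12) and 28–41% (WHO-DAS) would be called improved, and low scorers would seem to worsen by about 1.1–1.8 GHQ-12 points.

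The larger part of the false improvement is threshold noise, which would remain if the cut-offs were dropped. The selection effect is the smaller part and grows as more of the clinic population lies near or below the cut-offs.

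Confidence is high for the direction, which needs only reliability below 1, and low for the exact sizes. None of this shows that the programme lacks benefit, or that a response above 50% would be an artefact. It shows that the planned summaries cannot be read without a comparator that the same data could supply.

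**What to change.** In the Analysis paragraph of the Quantitative outcomes evaluation:

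- State as the main Aim 3 estimate the mean change from baseline at eight weeks and four months, with 95% CI, on each scale in all enrolled patients, for example from a mixed model of all three visits.
- Keep percent improved as a secondary result, and show beside it the percent worsening by the same amount.
- State that the mean change in low scorers will not be interpreted on its own.

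In Limitations, add regression to the mean and threshold noise. The random re-interviews already planned for checking reliability could help to indicate the size of measurement error.

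The cost is wording and analysis time; no new data, visits or patients are needed. A mean change in points is less intuitive than a percent improved, which is why the latter is kept. The change does not correct for natural course or for patients presenting when unwell, and these must remain stated limitations.

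### The minimum enrolment of 116 allows for drop-out only, not for patients below the baseline cut-offs, so at the 50% planning value it does not deliver ±10 points

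*Protocol*

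**What the plan says.** All of this stands in the Protocol, under Quantitative outcomes evaluation.

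- **Who is enrolled (Study Population/Recruitment).** "All consecutive adults presenting to the mental health clinics at the four selected health centers for an initial visit" and carrying a diagnosis are invited. No GHQ-12 or WHO-DAS score is required at entry.
- **Who is in the denominator (Analysis).** The group is restricted to patients scoring above 2 "on the WHO DAS-II (indicating non-zero baseline disability) and a score of" at least 3 on the GHQ-12. In that group, "we will calculate the percent of patients who experience clinically significant reductions in score (25% for the GHQ-12 and 20% for WHO-DAS-II Brief").
- **Planning value.** For the proportion improving, "we will assume this to be 50% (the most statistically conservative for sample size calculations"). The protocol expects the true figure to be higher.
- **Precision.** "A sample size of 96 patients will allow us to estimate these proportions and 95% confidence intervals with precision of" ±10.
- **Minimum.** "Assuming a drop-out rate of 20%, the minimum sample size for enrollment in the study will be 116".
- **Expected enrolment.** To allow stratified results, "we will enroll as many patients are willing to participate (an estimate of 300 patients").
- **Low scorers.** The same paragraph plans a separate analysis of mean score change for patients with low baseline scores.

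**The concern.** The precision statement refers to proportions that exist only in the subset above the cut-offs, so the 96 must be patients who are in that subset and have a follow-up score. The minimum of 116 counts everyone enrolled. Two losses lie between those counts: patients not followed, and patients enrolled below the cut-offs. The protocol allows for the first only. Yet it sets no score criterion at entry and plans an analysis for low scorers, so it expects the second loss too.

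These percentages summarise the primary outcomes, mental health status and daily functioning. If enrolment ended near the stated minimum, their intervals would be wider than the protocol promises, and the team would have no count during recruitment to warn them.

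**Working it through.** **Inputs from the protocol:** 95% two-sided interval (z = 1.96), proportion p = 0.50, target half-width d = 0.10, drop-out 20%, minimum 116, expected enrolment 300.

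**Assumed:** the share q of enrolled patients above the cut-offs, shown over a range because the protocol gives none. Drop-out is taken to be the same above and below the cut-offs. Patients are treated as independent.

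**1. Reproduce the 96.** n = z² p(1−p)/d² = 1.96² × 0.25/0.01 = 96.04. With 96 the half-width is 10.0 points. The stated figure reproduces and has no slack.

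**2. Reproduce the 116.** 96 × 1.20 = 115.2, rounded up to 116. To keep 96 after losing 20% of those enrolled, the divisor is 1 − 0.20: 96/0.80 = 120.

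**3. Precision at 116 if everyone qualifies.** 116 × 0.80 = 92.8 followed. Half-width = 1.96 × √(0.25/92.8) = 10.2 points.

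**4. Precision at 116 when only a share q qualifies.** Evaluable n = 116 × 0.80 × q, and half-width = 1.96 × √(0.25/n). The last column is 96/(0.80 × q), rounded up.

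| q (assumed) | Evaluable n at 116 enrolled | Half-width, points | Enrolment needed for 96 evaluable |
|---|---|---|---|
| 100% | 92.8 | 10.2 | 120 |
| 90% | 83.5 | 10.7 | 134 |
| 70% | 65.0 | 12.2 | 172 |
| 50% | 46.4 | 14.4 | 240 |

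**5. The expected 300.** 300 × 0.80 = 240 followed, and 96/240 = 0.40. So 300 enrolled meets ±10 if at least 40% are above the cut-offs.

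**6. Sensitivity to p.** If the true proportion were 70%, then at 116 enrolled q = 90% gives 1.96 × √(0.21/83.5) = 9.8 points, and q = 70% gives 1.96 × √(0.21/65.0) = 11.1 points.

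**The case against.** **The protocol does not plan to stop at 116.** It recruits consecutive patients over a calendar window, takes all who are willing, and expects about 300. This stands and limits the practical effect: 300 absorbs the loss down to a 40% qualifying share. It does not rescue the stated minimum. The 300 is an estimate, its stated reason is stratification, and 116 remains the figure tied to the precision.

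**The 50% is conservative.** Also true. With a true proportion of 70% and 90% qualifying, 116 gives about ±9.8. The shortfall is therefore a statement about the protocol's own planning value, not a claim that ±10 is out of reach at 116 whatever the result.

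**The qualifying share may be high.** These are diagnosed patients at an initial visit, and the WHO-DAS cut-off asks only for non-zero disability. If each scale uses only its own cut-off, instead of both jointly, the loss is smaller again. At 90% the shortfall is under one point. The 50% row illustrates the range and is not a forecast.

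**Patients who do not return are said to be included in the analysis.** They have no follow-up score, and the 20% inflation itself treats them as lost. If they were kept in the denominator, 116 would still need 96/116 = 83% to qualify.

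**A stronger reading: clustering.** A reader might infer that clustering within four health centers is a second reason why the minimum fails. The document does not support that. It gives no intraclass correlation, so any size would be assumed. The Executive Summary says the facilities are purposively selected, so they can be treated as fixed strata, and the Analysis paragraph already plans results by health center. The Limitations section also says results may not generalise across districts. What remains is a note that the intervals are conditional on these four centers.

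**Conclusion.** The point holds for the step from 96 to 116. The 96 is right as the number of followed patients above the cut-offs, and it would be wrong to infer that it was calculated for all enrolled patients.

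At the planning value of 50%, with 20% loss, the stated minimum does not deliver the stated precision. The shortfall is small if nearly everyone qualifies (±10.2 at 100%, ±10.7 at 90%) and material if many do not (±12.2 at 70%, ±14.4 at 50%). The drop-out formula accounts for 4 patients (120 against 116). The missing allowance for patients below the cut-offs accounts for the rest, and its size depends on a share that the protocol does not give. If about 300 enrol and at least 40% qualify, ±10 is met with patients treated as independent. A stated figure is therefore wrong and worth correcting, but the evaluation itself is not at risk if recruitment goes as expected.

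**What to change.** In the Analysis paragraph:

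1. State that 96 means patients with a follow-up score who were above the baseline cut-offs, and say whether each scale uses its own cut-off or both apply jointly.
2. Then either set the minimum at 120 baseline-positive patients (96/0.80), counted from the baseline form as recruitment proceeds, or keep 116 enrolled and restate the precision over a range of baseline-positive shares, as in the table above.
3. Say that the expected 300 meets ±10 if at least 40% are baseline-positive, with patients treated as independent.
4. As a secondary matter, add one sentence that the intervals are conditional on the four purposively selected centers.

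The cost is protocol wording and, with the first option, a running count from a form already collected. No extra patients are needed if about 300 enrol and at least 40% qualify. The downside is that the precision quoted at the minimum becomes slightly less favourable if 116 is kept.

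### The minimum enrolment of 116 does not leave 96 patients after the plan's own 20% drop-out; 120 are needed

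*Protocol*

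**What the plan says.** Everything relevant is in the Analysis paragraph of the Protocol's quantitative outcomes evaluation. The target quantities are the proportions of patients whose GHQ-12 and WHO-DAS scores fall by a clinically significant amount. With no prior information on these proportions, the plan writes "we will assume this to be 50% (the most statistically conservative for sample size calculations". The precision statement follows: "A sample size of 96 patients will allow us to estimate these proportions and 95% confidence intervals with precision of" ±10. Attrition is then allowed for: "Assuming a drop-out rate of 20%, the minimum sample size for enrollment in the study will be 116".

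Two further statements bear on the point. Actual recruitment is meant to go well beyond the minimum, so that outcomes can be stratified: "we will enroll as many patients are willing to participate (an estimate of 300 patients". On losses, the plan says: "Patients who do not return for follow up will not be re-interviewed but will be included in final data analysis". The inflation formula is not given.

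**The concern.** A drop-out rate is a fraction of those enrolled. To end with a required number after losing a fraction d, the required number is divided by 1 − d. The stated minimum looks like the required number multiplied by 1 + d, which always gives too few. If so, a study that recruited exactly its stated minimum and lost exactly its assumed 20% would finish below the 96 on which its precision statement rests. The three stated figures (96, 20% and 116) would then not fit together.

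**Working it through.** **Inputs**, all from the Analysis paragraph: assumed proportion p = 0.50; 95% two-sided confidence interval, so z = 1.96; half-width 0.10, reading ±10 as percentage points; drop-out d = 0.20; stated minimum enrolment 116; expected enrolment about 300.

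**Step 1: reproduce the base figure.** For a single proportion with a normal-approximation interval,

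n = z² × p(1 − p) / (half-width)² = 1.96² × 0.25 / 0.10² = 96.04.

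This agrees with the stated 96.

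**Step 2: reproduce the stated minimum.** 96 × (1 + 0.20) = 115.2, rounded up to 116. This matches the plan exactly. Because the plan prints no formula, the multiplication is inferred from the match.

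**Step 3: correct inflation.** 96 / (1 − 0.20) = 120. Carrying the unrounded 96.04 gives 120.05, so 121. Rounding the base up to 97 first gives 121.25, so 122. The plan itself uses 96, so 120 is the consistent figure.

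**Step 4: what 116 delivers.** The results below do not depend on how 116 was obtained.

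| Enrolled | Remaining after 20% loss | Half-width at p = 0.50 |
|---|---|---|
| 116 | 92.8 | 1.96 × √(0.25 / 92.8) = 10.17 points |
| 120 | 96.0 | 1.96 × √(0.25 / 96) = 10.00 points |
| 300 | 240.0 | 1.96 × √(0.25 / 240) = 6.33 points |

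The drop-out that 116 can absorb while keeping 96 is 1 − 96/116 = 17.2%, not 20%.

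**Step 5: chance variation in drop-out.** If each patient is lost independently with probability 0.20 (an assumption of this check), the number remaining is binomial. The probability that at least 96 remain is 0.270 with 116 enrolled and 0.554 with 120. The second figure is only a little above one half because 120 is set to give 96 on average.

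**The case against.** Four points can be made for leaving the number alone.

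- **The minimum is not the target.** The plan invites all consecutive eligible adults at four health centers, expects about 300, and nothing stops enrolment at 116. With 300, the half-width is ±6.3 points. This stands, and it is why the practical effect is small. But 300 is an estimate that depends on willingness to take part, and it is justified by stratification. The ±10 statement is tied to 96 and 116.
- **±10.17 rounds to ±10, and p = 0.50 is the worst case.** Also true. With 92.8 patients and p = 0.60, the half-width is 1.96 × √(0.24 / 92.8) = 9.97 points. There is no hypothesis test or power target here, so no error rate changes. The inconsistency remains all the same: 116 less 20% is not 96. The probabilities in Step 5 should be read in this light, since missing 96 by three patients costs only 0.17 points.
- **Patients who do not return are kept in the analysis.** This does not rescue 116. The outcome is a percentage reduction from baseline, which cannot be observed without a follow-up score, and this document gives no imputation rule. If such patients counted in full, no drop-out allowance would have been needed.
- **120 may not yield 96 either.** The proportions are calculated only among patients above the baseline cut-offs (WHO-DAS above 2, GHQ-12 of 3 or more). Neither 116 nor 120 allows for enrolled patients below them. This is correct, but it is a separate matter and only makes 116 shorter.

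**Conclusion.** The error is real. On the plan's own inputs the minimum should be 120, so the stated 116 is four too low. At 116 enrolled and 20% lost, about 93 patients remain and the 95% half-width at 50% is ±10.2 points instead of ±10.0. The consequence is small and vanishes if recruitment comes near 300, so this is a minor correction to a stated design figure and does not threaten the study.

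The conclusion rests on reading ±10 as percentage points, on counting only patients with a follow-up score, and on every enrolled patient meeting the baseline cut-offs. If some do not, the shortfall at 116 is larger.

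**What to change.** In the Analysis paragraph, do one of the following:

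- replace 116 with 120 and show the calculation, 96 / (1 − 0.20) = 120; or
- keep 116 and restate what it delivers: about 93 patients with follow-up and a precision of ±10.2 points at 50%.

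Whichever is chosen, it would help to say that the 96 refers to patients who meet the baseline cut-offs and have a follow-up score. With 300 enrolled and 20% lost, 96 / (300 × 0.80) = 40% of enrolled patients would have to meet the cut-offs to reach 96, if drop-out is the same above and below them.

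The cost is one number or one sentence in the protocol. Recruitment plans need not change, because about 300 patients are already expected.

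### The only regression planned for the two primary scales uses a yes/no percent fall from baseline; modelling the follow-up score itself would gain about 15 to 22 points of power at n = 240

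*Protocol*

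**What the plan says.** All of this is in the protocol, under Quantitative outcomes evaluation.

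- The outcomes and visits: "The primary outcomes will be mental health status and daily functioning, measured at first visit, eight weeks and four months". Baseline, eight-week and four-month scores are therefore sought on both scales.
- Among patients above a cut-off on each scale at baseline, the plan reports the percentage with "clinically significant reductions in score (25% for the GHQ-12 and 20% for WHO-DAS-II Brief").
- The model: "We will use multivariable logistic regression to identify covariates associated with improved scores". No covariate list follows.
- About 300 patients are to be enrolled, rather than the minimum of 116, so as to "stratify outcomes by characteristics such as age, gender, health center, diagnosis, and whether the patient is newly diagnosed or has previously been treated".
- Treatment history is available: "self-reported treatment status (new to treatment or received previous treatment) will be recorded".
- The score as a score appears only here: "Among individuals with low GHQ-12 and WHO-DAS-II Brief scores we will calculate within-person mean score change at eight weeks and four months".

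**The concern.** A logistic model needs a yes/no outcome, and the percent fall is the only one defined for these scales. Patients above the cut-offs, who are the group of main interest, therefore get no analysis of the score itself, although it is collected at three visits. This has two consequences.

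1. **Lost information.** A patient who just reaches a 25% fall counts the same as one who recovers fully. Real associations with age, diagnosis or treatment history become harder to detect.
2. **Dependence on the starting score.** The fall needed to count as improved is set by the baseline value. If new and previously treated patients start at different levels, treatment history can be linked to improvement through starting severity alone.

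The associations are also used elsewhere. The Executive Summary and the qualitative Data Analysis paragraph use the interviews to interpret and illustrate associations found quantitatively, so a missed or misread predictor would carry into that synthesis.

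**Working it through.** **The plan's own figure.** For a proportion of 50% with a 95% interval of ±10 points, n = 1.96² × 0.5 × 0.5 / 0.10² = 96.04, which matches the stated 96. This sizes the responder proportion. The protocol gives no power, effect size, SD or pre-post correlation for the regression.

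**Sample sizes used.** 300 less 20% dropout = 240 analysed, assuming all are above the cut-offs. 96 is the sized number.

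**Step 1: cost of dichotomising alone (closed form).** Take two equal groups, a two-sided 5% test and N = 240. The shift giving 80% power on a continuous score is d = (1.96 + 0.842) × √(4/240) = 0.362 SD. Cut at the median, the group proportions are Φ(−0.181) = 0.428 and Φ(0.181) = 0.572, and power for comparing them is 60.5%. The loss is 80 − 60.5 = 19.5 points. At improvement rates of 60%, 70% and 80%, power is 59.5%, 56.1% and 49.4%. The protocol expects a rate above 50%, where the loss grows. At N = 96 and a 50% rate, 80% falls to 59.9%.

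**Step 2: the planned outcome against a model of the score (simulation).** Assumptions, none from the protocol except the cut-off, the threshold and the approximate 50% rate: GHQ-12 scored 0–12, baseline mean 7, SD 3, baseline ≥ 3, a 50/50 binary covariate, improved if follow-up ≤ 0.75 × baseline. The comparator is a linear model of the follow-up score with baseline as covariate and robust standard errors. Monte Carlo error is about 2 points per figure. Power for a 0.3 SD effect at n = 240:

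| Correlation | Logistic, percent fall | Follow-up score with baseline | Gap |
|---|---|---|---|
| 0.3 | 43% (repeat run 46%) | 65% (68%) | 22 (22) |
| 0.5 | 56% (55%) | 78% (75%) | 22 (20) |
| 0.7 | 73% (75%) | 88% (90%) | 15 (15) |

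At n = 96 and correlation 0.5, power is 29% against 39% for 0.3 SD (gap 10), and 39% against 59% for 0.4 SD (gap 20). Across settings, and allowing for simulation error, the range is about 7 to 20 points.

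A separate simulation used other assumed scales (GHQ-like: mean 6.5, SD 2.5; WHO-DAS-like: 0–48, mean 20, SD 8) and an effect giving the score model about 80% power at n = 240. The loss was about 20 to 27 points at improvement rates of about 42–64%.

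**Step 3: where the loss comes from.** Adding baseline to the logistic model raises power by only about 0 to 5 points. The rest of the loss is due to dichotomising.

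**Step 4: dependence on baseline.** If the GHQ-12 is scored 0–12, a 25% fall needs 1 point from a baseline of 3–4 (0.75 to 1), 2 points from 5–8 (1.25 to 2) and 3 points from 9–12 (2.25 to 3). Suppose a covariate has no effect given an error-free baseline but its groups differ by 0.8 SD at baseline. At n = 240 the unadjusted logistic model is then significant in about 14–15% of studies at correlation 0.5 and 31–34% at 0.3. At correlation 0.7 there is no inflation.

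**Step 5: the same check with a baseline measured with error.** With assumed reliability of 0.7–0.8, the baseline-adjusted score model itself rejects in about 8–31% of studies, and the unadjusted logistic model in about 5–7%.

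**The case against.** The strongest replies are these.

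- **The protocol does not say that baseline is left out.** This is correct. The logistic model has no covariate list. The list of characteristics belongs to the stratification sentence and opens with an open-ended phrase. A covariate list is also commonly left to an analysis plan, which is not shown. A reader might infer that the model omits baseline; the text does not support that.
- **The power loss is not caused by a missing baseline term.** Also correct, as Step 3 shows.
- **Baseline adjustment is not a cure for bias.** Diagnosis and treatment history are not randomised. Step 5 shows that with measurement error the adjusted model can reject more often than the unadjusted logistic one. A reader might infer that adjustment restores the nominal error rate; that holds only for an error-free baseline.
- **The responder outcome is a legitimate target.** A group that meets the threshold more often is associated with improvement in the sense the protocol defines. This stands as a reason to keep the responder result, but not as a reason to have no model of the score.
- **The larger enrolment is not wasted.** The 300 patients are justified by stratified outcomes, and subgroup responder proportions are unaffected. The regression is exploratory, with no covariate hypothesis under Aim 3, and the Limitations section already restricts causal claims.
- **The simulated logistic model has one covariate, whereas the plan's is multivariable.** The exact figures would shift, but the cost of dichotomising does not arise from the number of covariates.

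**Conclusion.** The point holds as an inexpensive improvement in efficiency. The protocol itself fixes the model type and the dichotomised outcome, so this part does not rest on silence. Under the stated assumptions, modelling the score gains about 15 to 22 points of power at n = 240 for a 0.3 SD effect near a 50% improvement rate, and about 7 to 20 points at n = 96. The loss is larger at the higher rates that the protocol expects.

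The bias part is conditional. Associations from an unadjusted percent-fall model can reflect starting severity when groups differ at baseline and the pre-post correlation is low to moderate. It cannot be said that the planned model will be unadjusted, or that adjustment removes all bias. The sized responder proportion and its ±10 precision stand.

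**What to change.** In the Analysis paragraph of Quantitative outcomes evaluation, add a sentence to this effect: the GHQ-12 and WHO-DAS Brief scores at eight weeks and four months will each be regressed on the baseline score of the same scale plus age, gender, health center, diagnosis and prior treatment status, using a linear model with robust standard errors or a mixed model over both visits.

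Keep the percentages with a 25% or 20% fall as the descriptive headline. In any logistic model that is reported, include the baseline score as a continuous term.

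The cost is one sentence and one additional model per scale (per visit if the visits are fitted separately), with no new data, visits or patients. Three downsides should be stated in the text: coefficients are in scale points rather than odds of a clinically significant fall; floor effects are possible; and, because the groups are not randomised and baseline is measured with error, adjusted associations are exploratory and may carry residual bias.
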